## Abstract

**Background/Objectives: ***Cannabis sativa* (CS) exerts its effects through the endocannabinoid system. Although studies have shown limited evidence regarding the plant’s therapeutic efficacy, little is known about the standardization of doses and their corresponding effects. This study aims to analyze changes in muscle electrical activity and cardiovascular hemodynamics before, during, and after administering doses of full-spectrum cannabis and tetrahydrocannabinol (THC) oils. **Methods:** Participants will be assigned to a single group that will undergo five different interventions: CBD + THC at 12.50 mg, CBD + THC at 18.75 mg, THC intervention at 12.50 mg, THC at 18.75 mg, and placebo intervention (PI). The study will enroll healthy, self-reported men and women aged 18 to 50, with no mental health disorders and no exposure to CS in the past six months. Interventions will occur on five randomized days, following three phases: (1) pre-intervention (PRE-IN); (2) intervention (IN)—1 h after oral oil ingestion; and (3) post-intervention (POST-IN)—2 h 30 min after ingestion. At each stage, 2 min of quiet breathing (QB); 2 min with an inspiratory resistance valve (30% of maximal inspiratory pressure—PImax) and expiratory valve (10% of maximal expiratory pressure—PEmax) (VAL); and 4 min of recovery without the valve (REC) were evaluated. Register: RBR-3jsvtbr. **Conclusions:** This study will enhance the understanding of the dose–response effects of full-spectrum cannabis and THC oils and may serve as a model for future research in this field.

## 1. Introduction

The *Cannabis sativa* (CS) plant, commonly known as marijuana, is an illicit drug widely used throughout the world, primarily for recreational purposes. Its use dates back to the third millennium B.C. in India, where it was used primarily for medicinal purposes, including the treatment of malaria, constipation, pain, and dysmenorrhea. Over the centuries, its use spread throughout Central Asia and was included in various pharmacopeias worldwide, covering regions such as Asia, the Middle East, South Africa, and South America [1,2].

A major milestone in the history of cannabis occurred in 1964 with the isolation of its main active ingredient, delta-9-tetrahydrocannabinol (Δ9-THC). Prior to this, research on the plant was limited due to high variability in dosage and, consequently, its therapeutic effects. During this period, the plant was classified as dioecious, with the female flower identified as the main source of cannabinoids, from which various substrates are extracted to produce medicines [3].

The number of phytocannabinoids in CS is about 100, with the most well-known being Δ9-THC and cannabidiol (CBD) [4]. The effects of these compounds on the human body are attributed to the complex endocannabinoid system, which includes not only endocannabinoids synthesized internally but also cannabinoid receptors type 1 (CB1) and type 2 (CB2) present in various cells throughout the body. It also affects the enzymes responsible for the production and degradation of endocannabinoids [5,6]. THC acts as a partial agonist at CB1 and CB2 receptors within the endocannabinoid system, exerting its psychoactive and pain-modulating effects primarily through CB1 activation. In contrast, CBD has low affinity for the active sites of these receptors [7,8]. Therefore, CB1 receptors appear to be the most relevant for changes in muscle electrical activity and cardiovascular hemodynamics, as they are primarily located in the central nervous system and modulate both neural control of muscle contraction and autonomic cardiovascular responses.

Extracted from CS, tetrahydrocannabinol (THC) oil has been shown to interact with receptors present in the brain, significantly impacting the development of cannabinoid-based therapeutic drugs and their potential to alleviate symptoms of spasticity [9]. Cannabidiol (CBD) oil, on the other hand, is a non-psychoactive compound used in medicine for its antiepileptic, anti-inflammatory, antiemetic, antipsychotic, anxiolytic, and muscle relaxant effects [10].

Several studies suggest that CBD may offer therapeutic benefits in a wide range of conditions, mental psychological disorders, diabetes, gastrointestinal problems, cancer, oxidative stress, inflammation, and cardiovascular disease [11,12,13]. Also has shown that an acute dose of CBD can cause vasodilation and reduce blood pressure in humans, possibly through the activation of CB1 receptors [14]. In addition, CBD has been associated with improved myocardial dysfunction in models of diabetes [15]. However, there is still a significant lack of human studies investigating the effects of CBD on respiratory muscle and cardiovascular hemodynamics.

Research using lung tissue found that THC induced a concentration-dependent inhibition of cholinergic contraction in human airway smooth muscle cells through the activation of prejunctional CB1 receptors [16]. Based on this finding, Morris and coworkers [17] found a significant association between inhaled cannabis use and improvements in forced expiratory volume in the first second (FEV_1_) and forced vital capacity (FVC) in individuals with COPD.

Abdallah and collaborators [18] conducted a study to investigate whether a single dose of vaporized inhaled cannabis could relieve exertional breathlessness and improve exercise endurance, focusing on improving static and dynamic airway function in adults with advanced COPD. However, the results did not show any significant effects on lung function measured by spirometry, nor on exertional breathlessness during effort or exercise endurance capacity.

Overall, information on the pharmacokinetics and pharmacodynamics of cannabis-derived medications remains limited. However, a recent study using Spectrum Yellow oil 20 mg/mL of cannabidiol (CBD)/0.9 mg/mL Δ9-tetrahydrocannabinol (THC) found that a prudent approach to assessing tolerability includes initial doses of 240 mg of CBD and 10.8 mg of THC [19]. These findings highlight the importance of further research to better understand the effects of these compounds, thereby contributing to a safer and more effective approach to the use of cannabis-derived medications.

In addition, there is a lack of standardization regarding dosage and routes of administration. The drug exhibits high interindividual pharmacokinetic variability when administered orally, which may be influenced by demographic factors such as sex and weight [20]. These factors hinder the standardization of cannabis use and the identification of tolerability parameters, underscoring the need for studies comparing different doses and their effects in humans.

To achieve this goal, our study proposes a comprehensive approach designed to describe the potential changes and investigate the dose–response relationship to the acute effects of cannabis and THC oils in full-spectrum extraction. This study will be conducted in healthy individuals subjected to unidirectional respiratory overload and will assess cardiovascular hemodynamics and respiratory muscle electrical activity, allowing for a detailed examination of the effects of these compounds on different body systems and thus providing a more comprehensive understanding of their physiological effects. These data are crucial for future research and the development of treatments related to respiratory, cardiovascular, and muscular rehabilitation associated with medical cannabis. They also offer valuable insights into how these compounds can be used safely and effectively in clinical and therapeutic settings.

## 2. Materials and Methods

This is a randomized controlled crossover clinical trial with a 1:1:1 allocation ratio, double-blinded, which will be described according to the Consolidated Standards of Reporting Trials (CONSORT) criteria [21] where the checklist will be available in the online Supplementary Materials, and the protocol will follow the description suggested by the Standard Protocol Items Recommendations for Interventional Trials (SPIRIT) [22]. This study will be conducted at the Onofre Lopes University Hospital, of the Federal University of Rio Grande do Norte. The study was authorized by Brazilian Health Regulatory Agency (ANVISA) and was registered in the Brazilian Clinical Trials Registry—ReBEC, a public registry, under the trial registration number RBR-3jsvtbr, with the registration date of 30 April 2024.

### 2.1. Sample Size and Allocation

The sample size will be determined after a pilot study with five subjects, considering the cardiac output (CO) values as the main variable in intra- and inter-group comparisons through mixed model analysis of the Generalized Estimating Equations (GEE) test. An alpha error of 0.05 with a two-sided distribution and a test power of 80% will be established. Recruitment will be done through convenience sampling, using direct invitations and advertising on social media, posters, flyers on Instagram and WhatsApp, targeting the general population.

Participants will be randomly assigned to a single group, which will undergo five different types of interventions: (1) CBD + THC intervention at 12.50 mg (CBD + THC/12.50 mg), (2) CBD + THC at 18.65 mg (CBD + THC/18.65 mg), (3) THC intervention at 12.50 mg (THC/12.50 mg), (4) THC at 18.65 mg (THC/18.65 mg), and (5) placebo intervention (IP). The order of interventions for each individual will be randomized using the https://www.sealedenvelope.com website for analysis (accessed on 4 September 2025).

To conduct the five research interventions, we will use three different oils. The first is an THC oil with a concentration of 2.50 mg/mL “Naternal Full Spectrum Delta 9 THC”, from (Naternal^®^, Morrisville, NC, USA). The second is a Cannabis oil containing 50 mg/mL CBD and 1.83 mg/mL THC “Lazarus Naturals High Potency Full Spectrum” from (Lazarus Naturals^®^, Seattle, DC, USA). The third, used in the placebo intervention (IP), is an MCT (Medium Chain Triglycerides) oil used as a base for diluting the full-spectrum Cannabis and THC oils, consisting of 70% fractionated coconut oil and 30% corn oil.

During the THC evaluations, the mL dosages will be determined based on the concentration of the product. Similarly, in the evaluations of the CBD + THC intervention, the THC and cannabis oils will be combined to achieve an equal ratio of CBD and THC for each specific dose. In the placebo intervention, all participants will receive a dose of 5.00 mL of MCT. The dosages and corresponding values are detailed in Table 1.

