### 2.5. Outcomes

#### 2.5.1. Primary Outcome

Hemodynamic evaluation will be performed using the PhysioFlow^®^ device (Manatec Inc., Paris, France). It is a non-invasive cardiac output monitor that provides hemodynamic parameters through transthoracic electrical bioimpedance signal analysis. PhysioFlow measures changes in impedance by applying a high-frequency alternating current (75 KHz) with low amplitude (3.8 mA) through the chest. Two sets of electrodes (PhysioFlow OS-50, Manatec Biomedical, Macheren, France)—one transmitting and the other receiving the electric current—will be applied above the supraclavicular fossa at the left base of the neck and along the spinal line at the thoracolumbar transition. An additional pair will be used for continuous electrocardiographic monitoring, recorded as recommended by the manufacturer after shaving and cleaning the skin with alcohol, followed by abrasion with Nuprep^®^ (Weaver and Company, Aurora, CO, USA) gel.

The sEMG is used to acquire and process respiratory muscle activity, a non-invasive technique performed with the BTS FreeEMG 1000 (Milan, Italy) device from BTS Bioengineering, which performs all amplification and filtering signal processing. The signal is acquired using 4 sensors connected to 4 disposable electrodes (4 cm long, 2.1 cm wide and 2 cm between poles) placed on each muscle to be analyzed after proper skin preparation according to the appropriate positioning in the literature for better signal acquisition. The skin preparation will be done by shaving, cleaning with 70% alcohol, rubbing the skin with gauze and applying the electrodes in the direction of the muscle fibers, according to the SENIAM recommendations (1999) [27]. The analyzed muscles are: sternocleidomastoid (SCM), scalene (ESC), parasternal (PARA) and rectus abdominis (RA), all on the right side, positioned as follows at the lower third of the distance between the mastoid process and the sternoclavicular joint [28]; 5 cm from the sternoclavicular joint and 2 cm above this point [29]; at the second intercostal space and 3 cm from the sternum at the umbilical line, 4 cm from the umbilicus [30]. The data are acquired and stored by the BTS FreeEMG 1000 (BTS Bioengineering), which handles all amplification and filtering of the signal acquired by the 4 sensors. The collected signals are stored using the SmartCapture software (BTS Bioengineering, Milan, Italy) and analyzed using the SmartAnalyzer program version 1.10.470.0.

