### 2.7. Statistical Analysis

Normality and distribution of data will be assessed using the Shapiro–Wilk test. For descriptive analysis, we will use mean and standard deviation for parametric data and median and interquartile range for nonparametric data. Intra- and inter-group comparisons will be made using mixed model analysis, specifically the Generalized Estimating Equations (GEE) test, with adjustment for multiple comparisons using the Sequential Bonferroni correction in IBM SPSS Statistics version 25 (International, based in Armonk, NY, USA). Sample characterization data will be analyzed using GraphPad Prism 8.0 (GraphPad Software Inc., San Diego, CA, USA) for graph construction. A significant level of *p* < 0.05 and a 95% confidence interval (CI) are used for all analyses.

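### The sample size is planned for cardiac output at two-sided 0.05 with no multiplicity allowance, while the analysis applies Sequential Bonferroni and the primary outcome also covers other haemodynamics and four muscles

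*Protocol article*

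**What the plan says.** Section 2.1 defers the number of participants: "The sample size will be determined after a pilot study with five subjects, considering the cardiac output (CO) values as the main variable". The CO values are to be used in comparisons within and between interventions by generalized estimating equations (GEE), and the targets are "An alpha error of 0.05 with a two-sided distribution and a test power of 80% will be established". No N, CO difference, standard deviation, stage, breathing condition or target contrast is given, and no multiplicity allowance is mentioned.

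Section 2.7 analyses the same two kinds of comparison by GEE, with "adjustment for multiple comparisons using the Sequential Bonferroni correction", and uses p < 0.05 for all analyses. It does not say which contrasts, stages or outcomes make up the family being corrected.

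Section 2.5.1, whose heading is in the singular, covers two things. One is the PhysioFlow haemodynamic assessment as a group, where cardiac output appears only in the description of the device. The other is sEMG: "The sEMG is used to acquire and process respiratory muscle activity", recorded from four muscles.

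On the design, section 2.1 has one group receiving five interventions, and section 2.4 has three stages (PRE-IN, IN and POST-IN).

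**The concern.** Three stated elements do not fit together. The variable used for sizing is narrower than the declared primary outcome. The alpha used for sizing is not shown to be the alpha used for testing. The correction in the analysis has no stated family.

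This works in two directions. If N is set at 0.05 and CO contrasts are then tested at a corrected threshold, a real CO effect can be missed more often than the stated 20%. If the correction runs only among the contrasts within each outcome's model, nothing controls the error rate across CO, the other haemodynamic parameters and the four muscles. With no primary stage, breathing condition or contrast named, a reader could not tell which result the 80% power or the 5% error rate belongs to.

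**Working it through.** **Inputs.** From section 2.1: two-sided alpha 0.05, power 80%, five interventions. From section 2.4: three stages. From section 2.7: Sequential Bonferroni (Holm). The family size m is an assumption. The article gives no N, effect or SD, so there is no figure to reproduce and the check has to be scale-free (normal approximation).

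**Candidate families.**
- Each active intervention against placebo: m = 4.
- All pairs of five interventions: 5 × 4 / 2 = 10.
- All pairs of stage-by-intervention cells: section 2.4 appears to place PRE-IN once, on the first morning, as the reference for the later stages. That gives 1 + 5 × 2 = 11 cells and 11 × 10 / 2 = 55 pairs.

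**Power if N is set at unadjusted 0.05.** A contrast with 80% power at two-sided 0.05 has a standardised expected value of 1.960 + 0.842 = 2.802. At the first Holm threshold, 0.05/m, its power is Φ(2.802 − z), where z is the upper 0.025/m normal quantile. The factor on n that restores 80% is ((z + 0.842)/2.802)².

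| m | 0.05/m | z | Power at first step | Factor on n |
|---|---|---|---|---|
| 4 | 0.0125 | 2.498 | Φ(0.304) = 62% | 1.42 |
| 10 | 0.005 | 2.807 | Φ(−0.005) = 50% | 1.70 |
| 55 | 0.00091 | 3.317 | Φ(−0.516) = 30% | 2.20 |

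**Holm itself.** First-step power is a floor, because later steps use less strict thresholds. A simulation of the full procedure (200,000 runs; five within-participant conditions with equal variance and correlation; three effect patterns: one active intervention differs, all four differ equally, only the high doses differ) gave, for one given contrast, 62–71% with m = 4 and 52–54% with m = 10. Power to find at least one difference was higher: 63–89% with m = 4 and 80–90% with m = 10.

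**Error across primary outcomes.** Take five outcomes (CO and four muscles), each with a 5% error rate. If independent, the chance of at least one false positive is 1 − 0.95⁵ = 0.226. With an assumed equal correlation between the test statistics, simulation gives about 18% (correlation 0.5) or 15% (correlation 0.7). Counting further PhysioFlow parameters as primary would add to the number of outcomes.

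**Pilot input.** If the SD came from five values (4 degrees of freedom), the 95% confidence limits for the true SD would be √(4/11.14) = 0.60 and √(4/0.484) = 2.87 times the estimate. Pooling the within-participant residual over 5 × 5 = 25 pilot sessions gives up to (5 − 1) × (5 − 1) = 16 degrees of freedom, or 12 if period is also fitted. The 4-degree case is therefore a worst case, and section 2.1 does not say which applies.

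**The case against.** The strongest reply is that nothing has been computed yet. Section 2.1 defers N to the pilot, ties the sizing to the same GEE comparisons that section 2.7 corrects, and does not say whether its 0.05 is per comparison or family-wise. The sizing could still be done at the adjusted threshold. The contrast family may also be defined in an analysis plan that is not shown. This stands as far as it goes: the shortfall is conditional on sizing at unadjusted 0.05, which is the plain reading of section 2.1 but not the only one.

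Several stronger readings should be resisted:
- A reader might infer that the 80% power is definitely not achieved. Without N, effect or SD this cannot be shown.
- A reader might take ten contrasts as the minimum. Section 2.7 does not specify all pairs, and four contrasts against placebo also fit its between-intervention comparisons.
- A reader might count 5 × 3 = 15 cells and 105 pairs. Section 2.4 points to a single PRE-IN assessment, so 55 is the better-supported count if all cells are compared, although the three-stage wording leaves some doubt.
- A reader might quote 50% as the power for ten pairs. Under Holm it is a floor, and power for at least one difference was 80–90% in the scenarios run.
- A reader might conclude that a false-positive primary outcome is likely. A figure of 23% under independence, and less under positive correlation, does not say that.

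Factorial (dose by CBD) contrasts, a trend test over dose and an upper confidence limit for the SD are design preferences. Their absence is not an error. What remains is that one variable at 0.05 is used for sizing, while several comparisons and outcomes are tested.

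**Conclusion.** The mismatch is real and is more than detail left to another document: sections 2.1, 2.5.1 and 2.7 each state something, and together they do not support one power or one error rate. If N is computed at unadjusted 0.05, a given CO contrast would have less than 80% power under every family considered: at least 62% for 4 contrasts, 50% for 10 and 30% for 55. Across primary outcomes no control is described, with at most about 23% family-wise error for five independent outcomes and less if they are positively correlated. These sizes rest on the normal approximation, on assumed families, on the unadjusted reading of section 2.1 and on the correction acting within each outcome's model.

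**What to change.** Make the change before N is set.

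1. Name CO at one stage and in one breathing condition as the sole primary endpoint, with one primary contrast tested at two-sided 0.05, and size the trial for that contrast.
2. Alternatively, if several CO contrasts are to stay primary, list them as the Sequential Bonferroni family and compute N at its first threshold (about 1.42 times the unadjusted n for 4 contrasts, 1.70 times for 10), or restate the power for a given contrast.
3. In either case, move the other PhysioFlow parameters and the sEMG outcomes to secondary, and state whether the correction runs within or across outcomes.
4. Base N on a CO difference fixed in advance and on the within-participant variance pooled over all pilot sessions, not on the effect observed in five people.

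The cost is wording only at this stage. The downsides are that sEMG loses primary status and that the computed N may rise if several contrasts are kept.

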### 2.2. Eligibility Criteria

The study will include self-reported healthy Brazilian adults aged 18 to 50 years, with a body mass index (BMI) between 18.5 and 29.9 kg/m^2^, without respiratory dysfunction (i.e., forced vital capacity [FVC] > 80% and a ratio of forced expiratory volume in one second [FEV_1_] to FVC > 0.7 or >85% of predicted) [23], no uncontrolled or untreated mental disorders, no diagnosed cardiovascular disease, no history of arrhythmias or hypertension, no regular medication use, and no cannabis exposure in the past six months, and no history of substance abuse.

Participants will be excluded from the study if they withdraw, are unable to understand or complete any part of the study, or exhibit clinical instability during the procedures (i.e., heart rate > 85% of maximum heart rate, hypertensive peak with systolic blood pressure > 180 and/or diastolic blood pressure > 110 mmHg, hypertensive crisis with blood pressure > 190/90 mmHg or 175/115 mmHg). Pregnant women are also excluded.

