For all stages of respiratory Intervention (PRE-IN, IN and POS-IN) the data will be recorded for 8 min: 2 min of quiet breathing (QB), 2 min of breathing with inspiratory resistance at 30% of PImax and expiratory resistance at 10% of PEmax (VAL) using the BigBreathe^®^ valve (IMT/PEP, GHINNOTEK, Busan, Republic of Korea), followed by 4 min of recovery with spontaneous breathing (REC), as illustrated in Figure 1. During the 8 min of data collection, systolic blood pressure (SBP) and oxygen saturation (SaO_2_) will also be assessed, in addition to the Borg scale for mouth fatigue and dyspnea.

Except for the baseline stage, the other evaluation moments will take place exclusively in the afternoon. The study design can be better observed in Figure 2. Upon arriving at the research site, the participant will sit for the placement of electrodes and will then be taken to a bed, where they will be informed about the start of the pharmacological intervention. The respective oil, previously delivered by the responsible researcher following randomization, will be administered. Under the researcher’s guidance, the participant will be asked to wear a blindfold to cover their eyes and use a nasal clip to avoid any identification of the oil administered, open their mouth, and lift their tongue for the dose in drops. After the administration, the researcher will instruct the participant to remain seated and at rest. After 60 min, the second stage (IN) will take place and after 2 h and 30 min post-administration of the drug, the third evaluation stage (POST-IN) will begin.

The BigBreathe^®^ device will allow bidirectional threshold overload (IMT/PEP, GHINNOTEK, Busan, Republic of Korea) with an IMT range of 10–40 cmH_2_O and PEP of 5–20 cmH_2_O, with a resolution of 2 cmH_2_O. A variable load can be set on the IMT/PEP device, providing independent resistance to inspiration or expiration using two spring-loaded one-way valves. These valves only open when the pressure generated by the individual exceeds the spring tension set during inspiration and expiration, with simultaneous IMT and PEP effort in a single respiratory cycle [26]. A load of 30% of PImax and 10% of PEmax will be established for each participant, as previously described, as initial loads for respiratory muscle training, aiming only to activate the musculature while also considering the participant’s 45° trunk position.

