#### 2.5.2. Secondary Outcomes

Anthropometric data (height, weight, BMI) and an initial assessment form including age, sex, marital status, occupation, smoking, alcohol use, medication use, sleep duration in hours per day, presence of chronic diseases, heart disease, lung disease, psychological or psychiatric diagnosis, and previous cannabis use, including oil, will be collected from all subjects.

The initial assessments will include a clinical evaluation, covering vital signs (temperature, pulse, blood pressure, respiration, and heart rate) as well as the Hamilton Anxiety Scale (HAM-A) (Hamilton M, 1959) [31] to assess the presence and severity of anxiety symptoms in participants. The HAM-A consists of 14 items, each defined by a set of symptoms that measure both psychological anxiety (restlessness and psychological distress) and somatic anxiety (physical complaints). Each item is scored on a scale from 0 (none) to 4 (severe), with a total score ranging from 0 to 56, with a score below 17 indicating mild anxiety, between 18 and 24 indicating moderate severity, and between 25 and 30 indicating moderate to severe anxiety [31].

The Borg scale and dyspnea are also used, along with other monitoring measures such as respiratory rate (RR), heart rate (HR), and peripheral oxygen saturation (SpO2), which are monitored and recorded every 2 min during the PRE-IN, IN, and POST-IN phases.

During spirometry, the following variables are evaluated: Forced vital capacity (FVC), forced expiratory volume in one second (FEV_1_), forced expiratory flow between 25% and 75% of the FVC curve (FEF_25–75%_), and FEV_1_/FVC ratio. The evaluation is considered complete when three acceptable curves have been performed with two reproducible results according to the American Thoracic Society (ATS) and European Respiratory Society (ERS) guidelines [32]. The equipment used is a KoKo DigiDoser^®^ digital spirometer (Longmont, CO, USA) connected to a computer with the device’s own software, and calibration is performed daily by injecting a volume of air with a 3-L calibration syringe. The best spirometric values are selected for analysis. The values obtained will be compared with the relative and absolute values for the Brazilian population [33].

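### Withdrawal, non-completion and high heart rate or blood pressure are treated as exclusion from the study; applied to the analysis, this selects participants on variables close to the primary outcome

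*Protocol article*

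**What the plan says.** The rule stands in Section 2.2 (Eligibility Criteria) of the protocol article: "Participants will be excluded from the study if they withdraw, are unable to understand or complete any part of the study", or if they "exhibit clinical instability during the procedures (i.e., heart rate > 85% of maximum heart rate, hypertensive peak with systolic blood pressure > 180" mmHg. The list continues with "diastolic blood pressure > 110 mmHg, hypertensive crisis with blood pressure > 190/90 mmHg or 175/115 mmHg". The same paragraph excludes pregnant women.

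Section 2.4 places randomisation in the first morning session, alongside baseline and PRE-IN assessment and before any oil is given. Each participant is then due to receive all five interventions.

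The outcomes lie close to the triggers:
- Section 2.1 plans the sample size "considering the cardiac output (CO) values as the main variable".
- Section 2.5.1 (Primary Outcome) describes the device: "It is a non-invasive cardiac output monitor that provides hemodynamic parameters through transthoracic electrical bioimpedance signal analysis". Surface electromyography is in the same section.
- Section 2.5.2 lists "respiratory rate (RR), heart rate (HR), and peripheral oxygen saturation (SpO2), which are monitored and recorded every 2 min" among the secondary outcomes.
- Section 2.4 adds that during the 8-minute recordings "systolic blood pressure (SBP) and oxygen saturation (SaO_2_) will also be assessed".

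Section 2.7 names "mixed model analysis, specifically the Generalized Estimating Equations (GEE) test" and states no rule for the data of excluded participants.

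**The concern.** An eligibility criterion should be decidable before randomisation. Apart from pregnancy, the events in this paragraph mostly are not. They arise during the sessions, and three of them (withdrawal, non-completion, a limit crossed) can be consequences of an intervention. Pregnant women are ineligible and never enter the sample, so using the same word for both groups invites the reading that the others also leave the sample.

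If the rule is carried into the analysis, three things follow.
- **Selection on the outcome.** Heart rate is a component of cardiac output (heart rate times stroke volume), and the limits act only upward. Participants would be kept or dropped partly on the quantity being compared.
- **Loss of whole participants.** In a five-session crossover, one event would also remove that person's other sessions, including placebo. Taken literally, not completing any part has the same result.
- **Loss of tolerability evidence.** The article presents the trial as informing tolerability and dose–response. Participants who cross a haemodynamic limit are part of that evidence.

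Unweighted GEE does not correct for this, because it assumes that missingness is unrelated to the response.

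**Working it through.** The article gives no sample size, effect size, variance or expected exclusion rate, so there is no figure to reproduce. The sizes below are illustrations on stated assumptions.

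**1. When can the events occur?** Randomisation is in the first morning session. The limits apply during the procedures, which include the day-1 strength and ventilation manoeuvres, PRE-IN, the valve phase and the placebo day. Most events therefore follow randomisation, but not all follow active oil.

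**2. Simulated crossover.** Assumptions: 400,000 participants; five treatments; outcome = participant level (SD 1) + treatment effect + participant-specific response shared by the active oils (SD 0.6) + residual (SD 0.7). True effects against placebo are +0.5 and +0.8. A marker M = ρY + √(1−ρ²)·noise (noise SD √(1² + 0.7²) = 1.22) has one upper limit, set so that the stated share of participants cross it in at least one session. Share of the true effects (+0.5 / +0.8) recovered with ρ = 0.8:

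| Participants crossing | All their data removed | Data kept before the event session only | Data kept through the event session |
|---|---|---|---|
| 1% | 99% / 99% | 99% / 99% | 100% / 100% |
| 5% | 94% / 96% | 95% / 95% | 98% / 100% |
| 10% | 89% / 92% | 90% / 92% | 97% / 99% |
| 20% | 81% / 87% | 82% / 86% | 94% / 98% |

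With ρ = 0.5 and all data removed, recovery is 96% / 97% at 5% and 93% / 95% at 10%. Most of the protection comes from keeping the event session itself. The last column assumes that session was fully measured.

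**3. Direction.** With true effects of −0.5 / −0.8, the same rule gives −0.51 / −0.81 at 5% and −0.52 / −0.82 at 10%, a slight exaggeration.

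**4. Sensitivity to response variation.** I reran the model with the participant-specific response SD set to 0 instead of 0.6, all data removed and 10% excluded. Recovery is 98% / 98% for raising effects and 97% / 97% for lowering ones. So the 8–11% loss, and the exaggeration in step 3, depend on participants differing in their response.

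**5. How often might the heart-rate limit be crossed?** The article gives no formula for maximum heart rate. Assuming 220 minus age, the limit is 0.85 × (220 − 35) = 157.25 bpm at age 35 and 0.85 × (220 − 50) = 144.5 bpm at age 50. Take a resting rate of 70 bpm and a normally distributed rise, so that P = 1 − Φ((limit − 70 − mean rise)/SD):
- Mean rise 20, SD 20: z = 67.25/20 = 3.36, P = 0.04% at age 35; z = 54.5/20 = 2.73, P = 0.3% at age 50.
- Mean rise 40, SD 20: z = 47.25/20 = 2.36, P = 0.9%; z = 34.5/20 = 1.73, P = 4.2%.

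These are per session. Over four active sessions the chance is at most four times as large: about 0.2% and 1.3% in the first case, 3.6% and 17% in the second. Blood-pressure crossings are not included.

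**6. The blood-pressure limits.** The peak is defined by systolic > 180 and/or diastolic > 110 mmHg, the crisis by > 190/90 or 175/115 mmHg. One crisis pair has a systolic value below the peak limit, and the other has a diastolic value below it, so the categories overlap without a clear order.

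**The case against.** The strongest reply is that the sentence is a safety stop in a condensed article. It does not say that collected data are deleted, and Section 2.7 imposes no completer or per-protocol restriction. Analysis sets are commonly left to a fuller document. That stands to this extent: deletion is one reading, not a stated plan. It does not remove the point, because the article states a rule here, in the eligibility section, and the rule can be read either way. That choice should not be made after the data are seen.

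A reader might infer more than the documents support:
- **That the largest drug responders are removed.** Limits can be crossed before dosing, under the valve or on placebo, and blood pressure is not cardiac output.
- **That drug effects are always biased downward.** This is not so for effects that lower the outcome, and the Introduction itself cites a blood-pressure reduction with CBD.
- **That a 10% exclusion would remove 39% of a 0.5 SD effect.** That comes from truncating one intervention's mean, φ(1.2816)/0.90 = 0.1755/0.90 = 0.195 SD, and 0.195/0.5 = 39%, with the comparator untouched. Here the participant's placebo session would go too, so much of the shift cancels; the simulated loss is 8–11%.
- **That tolerability would go unreported.** Section 2.6 plans monitoring throughout, and Section 2 commits to CONSORT reporting. Neither passage, however, says that events will be tabulated by intervention.
- **That GEE must be replaced.** It need not be.

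The low expected event rate is also a fair objection. Participants are healthy, without hypertension or arrhythmia, and recorded semi-recumbent.

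**Conclusion.** The point holds in a limited form. Section 2.2 lists mostly post-randomisation events as grounds for exclusion from the study. If this is applied to the analysis, it selects completers on variables close to the primary haemodynamic outcome and discards their other sessions. Raising effects would be attenuated. Lowering effects would be slightly exaggerated if response varies between participants as assumed, and slightly attenuated if it does not.

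The size is not derivable from the article. On the assumed variances and a marker correlation of 0.8, removing all data costs about 1% of a true effect at 1% excluded, 4–6% at 5% and 8–11% at 10%. It costs less with a weaker correlation or a more uniform response. With a mean heart-rate rise near 20 bpm, crossings of the heart-rate limit would be rare and the bias small. Withdrawal and non-completion have no stated rate and could matter more. The planned number of participants is still open, pending a five-person pilot, so a few exclusions could weigh more heavily than these large-sample averages suggest.

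**What to change.** Leave the clinical limits and their consequences for procedures to the investigators, and separate them from the analysis rule:

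1. Move these events out of the eligibility section. State that a limit crossing, a withdrawal or an incomplete part may end further procedures but does not remove the participant from the analysis.
2. Analyse all randomised participants with at least one dosed session, using all data up to and including the event.
3. Report limit crossings and withdrawals by intervention and by stage (PRE-IN, IN, POST-IN).
4. Keep GEE as the main analysis. Add one sensitivity analysis for the missing sessions: weighted GEE with the recorded heart rate and blood pressure in the weight model, or a likelihood-based mixed model.
5. Have the investigators reconcile the overlapping blood-pressure limits.

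Items 1 to 3 and 5 change wording and tables only. Item 4 adds a little analysis work. The remaining cost is slightly unbalanced data. The rule should be fixed before any outcome data are analysed.
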